#### Statistical methods

Data were analyzed with SPSS version 23 (SPSS Inc., Chicago, Ill., USA) using analysis of variance (ANOVA), independent *t*-test, and other tests. Generally, if the mean score of variables before the intervention was significantly different between the intervention and control groups, the ANOVA test was used; otherwise, we used an independent *t*-test. The independent samples *t*-test (or the Mann-Whitney *U* test) was used to determine differences in numerical variables between the intervention and control groups. To draw a within-group comparison, we used the paired-sample *t*-test or its nonparametric equivalent, the Wilcoxon test. If necessary, missing data were examined at each time point and handled with an appropriate imputation method. All data of the full protocol and intervention study were potentially shareable after unidentified individuals. All researchers could access the data upon request to the Vice-Chancellor for Research and Technology of Hamadan University of Medical Sciences.

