### Sample size and eligibility criteria

According to previous studies, the intervention’s minimum effectiveness is 20% [35–37], referring to changes in the PMW construct, behavior, and SAML. Also, because of considering these cultural differences in the intervention’s minimum level of effectiveness, 20% was considered for intervention effectiveness based on the previous study with the same field and approach; taking into account the clustering coefficient of 1.5, alpha 5%, and 90% desired power, we need 54 people per group. Also, considering the 20% probability of attrition in the intervention process, the present study’s sample size was 116, including 58 in the experimental group and 58 in the control group.$$n=\frac{\overline{p}\left(1-\overline{p}\right){\left({Z}_{\beta }+{Z}_{\alpha /2}\right)}^2}{{\left({p}_1-{p}_2\right)}^2}$$

Inclusion criteria were access to the internet and social media apps (such as WhatsApp, Telegram, and Instagram), being a student in one of the universities in the city of Hamadan, and willing to participate in the study. Before participation, students signed written informed consent forms to participate in this study. The Principal Investigator will access consent forms of student participant data that will be nameless. Also, according to the consent form, students were free to withdraw from the study at any time.

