#### Randomization

Randomization was performed using a stratified random sampling procedure; individuals were assigned to 2 intervention and control groups. Randomization was performed after students signed informed consent, as well as the approval of universities to perform the study.

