### Measures

#### Student measures

Students completed questionnaires at 2-time points: a pretest and a 3-month follow-up (Fig. 1). The student questionnaire, containing approximately 100 items, covered substance abuse behavior based on PWM variables outcomes (e.g., attitudes, normative beliefs, behavioral intentions, and willingness), self-reports of the SAML Scale (SAMLS), and process evaluation. In addition, demographic questions comprised age, education level, socioeconomic status, sex, gender, parental education level, marital status, name of university, schools and courses, history of smoking and alcohol consumption, addiction status in parents, close friends, substance abuse status, internet access, amount of social media exposure and use of social media, and motivation to use social media.

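### The between-group test is chosen by a significance test on pretest scores, and neither named branch clearly adjusts for baseline

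*Protocol article*

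**What the plan says.** All of the analysis text is in Statistical methods. It lists the methods as "using analysis of variance (ANOVA), independent *t*-test, and other tests". It then gives a rule for the comparison of arms: "if the mean score of variables before the intervention was significantly different between the intervention and control groups, the ANOVA test was used". Where the pretest means do not differ significantly, the rule falls back on the two-sample t-test. The next sentence says, without any condition, that the independent t-test or the Mann-Whitney test "was used to determine differences in numerical variables between the intervention and control groups". The pretest enters directly in one other place: "To draw a within-group comparison, we used the paired-sample *t*-test or its nonparametric equivalent, the Wilcoxon test".

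The section names no covariate, ANCOVA, change score or repeated-measures model. It does not say whether the between-group tests are run on follow-up or change scores.

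Two facts from elsewhere matter. There are two arms (Randomization: "individuals were assigned to 2 intervention and control groups"), and a pretest is planned for every student (Student measures: "Students completed questionnaires at 2-time points: a pretest and a 3-month follow-up").

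**The concern.** This is a stated decision rule, so it cannot be excused as detail left to an analysis plan. There are two problems.

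- **The gate.** In a randomised trial, a baseline significance test asks whether a difference known to arise by chance is larger than chance usually gives. Its answer then picks the analysis, separately for each prototype-willingness construct and for the media literacy scale.
- **The branch behind the gate.** ANOVA, as named, does not remove a baseline difference when only two groups are compared.

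At stake are the protection that the rule was written to give and, more generally, precision in a trial of 116 students. If neither between-group branch adjusts, attention may also drift to the within-group paired tests, which cannot show an effect against control.

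**Working it through.** **Inputs.** From the article: two arms, pretest and 3-month scores, alpha 5%, 54 per group needed, 58 per group planned, 20% attrition. Assumed: pre-post correlation r of 0.3, 0.5 or 0.7; a true difference of 0.5 SD; normal scores; no clustering; 46 per arm (58 × 0.8 = 46.4). The article gives no figure for this analysis that could be reproduced. Its sample size rests on a formula for proportions, so the 0.5 SD is not the plan's effect.

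**Step 1: the two branches, read literally.** With two groups, F = t². In a simulated 58 + 58 example, t² = F = 2.4950 and both tests give p = 0.11698. The two branches are one test.

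**Step 2: error when the gate fires.** With no effect, the follow-up z-statistic given the baseline value z₀ has mean r·z₀ and variance 1 − r². Given a significant baseline difference, the mean of |z₀| is about 0.05845/0.025 = 2.34. For r = 0.5 the shift is 1.17 and the SD is √0.75 = 0.866. The chance of exceeding 1.96 is then about P(Z > (1.96 − 1.17)/0.866) = P(Z > 0.91), or 18%. The same approximation gives about 10% at r = 0.3 and 33% at r = 0.7. Simulation agrees to within about a point (table).

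**Step 3: power.** Unadjusted, the expected z is 0.5 × √(46/2) = 2.40, so power is about P(Z > 1.96 − 2.40) = 67%. ANCOVA divides the residual variance by 1/(1 − r²), that is, multiplies it by 0.91, 0.75 or 0.51. Expected z becomes 2.51, 2.77 or 3.36, and power about 71%, 79% or 92%. Simulation, which uses the t distribution, gives about one point less.

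| | r = 0.3 | r = 0.5 | r = 0.7 |
|---|---|---|---|
| *46 per arm* | | | |
| No effect, baseline significant: unadjusted test rejects | 10% | 19% | 32% |
| Same trials, ANCOVA rejects | about 5% | about 5% | about 5% |
| Power, unadjusted | 66% | 66% | 66% |
| Power, ANCOVA only if baseline significant | 66% | 67% | 68% |
| Power, ANCOVA always | 70% | 78% | 91% |
| *54 per arm* | | | |
| Overall type I error, unadjusted | 5.0% | 5.0% | 5.0% |
| Overall type I error, ANCOVA only if baseline significant | 4.7% | 4.3% | 3.6% |
| Power, unadjusted | 73% | 73% | 73% |
| Power, ANCOVA only if baseline significant | 73% | 74% | 75% |
| Power, ANCOVA always | 77% | 84% | 95% |

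**Step 4: why the gate forfeits the gain.** At 54 per arm and r = 0.5, the unadjusted test has 73.7% power in the 95% of trials with no significant baseline difference, and ANCOVA has 82.9% in the other 5%. So 0.95 × 73.7 + 0.05 × 82.9 = 74.2%, against 84% with ANCOVA throughout.

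**The case against.** Three points on the other side have force.

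- **The meaning of ANOVA is not certain.** A separate test kept for imbalance suggests loose wording for ANCOVA or a repeated-measures model, and the text begins with a general qualifier and allows for other tests. A change-score or repeated-measures analysis would use baseline, and the F = t² argument on follow-up scores would not describe it. This stands, so the lack of adjustment is conditional on the literal reading. The gate is not rescued. Change scores are also the weaker choice: at 54 per arm they give 59%, 73% and 92% power, against 77%, 84% and 95% for ANCOVA.
- **The error rates in Step 2 are conditional.** A reader might infer that the trial runs a false-positive risk of 19% or 32%. It does not. Those rates apply to the roughly 5% of comparisons with a significant baseline difference, and the overall rate stays at 5% or below under the literal and ANCOVA readings.
- **The size depends on assumptions.** At r = 0.3 the power gain is only about 4 points.

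A reader might also infer that the pretest is never used. The text does not support that: the pretest drives the gate and enters the within-group tests. What can be said is that no named between-group analysis clearly uses it as a covariate.

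**Conclusion.** The point holds in this limited form. The choice of between-group test rests on a baseline significance test, which is a poor rule whichever way ANOVA is read. Literally, it does nothing about imbalance, and the comparison is conditionally biased in the very case that it was meant to handle. Read as ANCOVA, it gives up nearly all the gain. The trial-level test remains valid. The general harm is lost precision: 4, 12 or 25 points of power against the unadjusted test at r = 0.3, 0.5 or 0.7, for an assumed 0.5 SD difference and 46 per arm. At r = 0.5, ANCOVA on 46 per arm is worth about 46/0.75 = 61 per arm unadjusted. Clustering is ignored in these figures.

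**What to change.** Delete the baseline significance test and the unconditional t-test sentence. For every score, prespecify one ANCOVA of the 3-month value on arm, that score's pretest value and the randomisation stratum, and report the adjusted mean difference with its 95% CI. State in advance what replaces the Mann-Whitney option if residuals are badly skewed, for example a bootstrap interval for the same adjusted difference. Keep the within-group paired tests as description only.

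This model is right if students were randomised individually within strata, as Participant characteristics and Randomization describe. The Methods paragraph of the abstract places randomisation at university and school level, and the sample size applies a clustering coefficient of 1.5. Those accounts must be reconciled first. If schools or universities were allocated, the baseline-adjusted model must also account for clusters.

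The cost is a few sentences. No new data are needed, and the SPSS version already named fits ANCOVA. If outcomes have already been compared by arm, report the change as made after the fact.

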#### Oversight and monitoring

As mentioned previously, this study was performed to complete the SMART model’s sixth and seventh stages, including the implementation of intervention and evaluation. Confidentiality was assured to all participants. Participants were randomly given ID numbers to be used in the education program. The list of names and ID numbers was confidentially kept on a secure server, only accessible to the principal investigator and administration staff (skilled in the ethical study). After completing the follow-up period, the data collection was completed. Students completed the number of answer questionnaires. Identifying information could not be shared by the students; thus, ID numbers were used in place of names in chat rooms and to receive education programs. As this study was a minimal-risk study, the occurrence of any adverse events was reported to the Principal Investigator and the Research Ethics Committee of Hamadan University of Medical Sciences to make the final decision on whether or not to continue the trial.

The possibility of serious adverse events was evaluated within 24 hours, and any other challenges were considered within 72 h, reporting to the Research Ethics Committee of Hamadan University of Medical Sciences within 2 weeks. The procedure of auditing was checked by the Principal Investigator 3 times, including drafting the proposal, conducting the study, and ending the study.

#### Ethics and dissemination

All university students were recruited for this study by the Research Ethics Committee of Hamadan University of Medical Sciences. All participants were voluntarily enrolled in this study. The researcher’s contact information was printed on the forms in case students had questions about the study. Also, this study was approved by the Research Ethics Committee of Hamadan University of Medical Sciences (code: 9811018459; ID: IR.UMSHA.REC.1398.827).

#### Sharing plan

All data is potentially shareable after unidentified individuals. All researchers could access the data upon request to the Vice-Chancellor for Research and Technology of Hamadan University of Medical Sciences. It is worth noting that results from this study will be prepared for publication in scholarly journals and updated on https://www.irct.ir/.

#### Confidentiality

As it was mentioned before, confidentiality was assured to all participants in all processes of the implementation procedure and monitored until the end of education programs. Participants were randomly given ID numbers to be used in the education programs. The list of names and ID numbers was confidentially kept on a secure server, only accessible to the Principal Investigator and administration staff (skilled in the ethical study). Also, the Principal Investigator checked the coding, security, and storage of data.

## Discussion

SAML and substance abuse prevention education programs must be carefully evaluated to ensure that they effectively enable people in youth health and media literacy skills, mainly about substance abuse behavior in the new media ecology and unique “Infomedia” ecosystem digital societies. To our knowledge, the SAML education programs being evaluated in this study can be the first web-based education program in universities; no prior research has psychometrically considered SAML in students who are among the high-risk groups regarding drug use. The study design, obviously including students’ data collection, allows for evaluation of the program’s immediate effects on student outcomes and any behavioral effects during the 3 months after the students receive the program. Also, gathering student feedback will help determine the chance of program implementation by universities.

We conclude that despite numerous advantages, internet-based educational intervention has some challenges; for instance, in the present study, the amount of time/response burden may be imposed on students. Concerning different effective factors and examining important constructs of PWM, the researchers had no options except for using a 100-item pre-post measure. Thus, this number of items could be considered a limitation. Therefore, web-based approaches may become an important new approach to reducing respondent burden. Also, it should be regarded that this intervention study will focus on specific social media and not traditional media channels. So, future study concerning all media platforms was recommended.

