**Methods:**

The present study evaluates an intervention program based on media literacy on substance abuse prevention among students using an integrated social marketing approach. This study aims to complete the SMART model’s sixth and seventh stages, implementing intervention and evaluation. Participants will be students of Hamadan University, Iran. Randomization will occur at the university and school levels, and gathered data will appear at two-time (i.e., pre-test and three months follow-up). Intervention group students will obtain both substance abuse prevention education and substance abuse media literacy (SAML) education between pre-test and 3 months post-test. Students in the delayed intervention will be given this education after study accomplishment; this group will receive their regular courses except for substance abuse prevention and media literacy titles during education intervention. The outcome variables are intentions and substance abuse behavior based on prototype willingness and substance abuse media literacy.

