## Methods/design

### Aim, design, and setting

The study design evaluated web-based randomized controlled trial substance abuse prevention and SAML education programs. It was expected that 3 universities (including Hamadan University of Medical Sciences, Hamadan Islamic Azad University, and Bu-Ali Sina University) would take part in the study. Data were collected from students at 2-time points (i.e., pretest and 3-month follow-up). Interventional research was based on the Social Marketing Assessment and Response Tool (SMART) pattern.

SMART is the operational model of social marketing in the field of health, which is used to improve the behavior of society and includes 4 stages as follows: (1) preliminary planning, (2) formative research (customer analysis, market analysis, and channel analysis), (3) production of interventions, materials, and pretests, and (4) intervention and execution (Fig. 2).

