**Fig. 3 Fig3:**
[figure not shown]
Template of SPIRIT recommended content for the schedule of enrolment, interventions, and assessments

Disincentive students received a gift card of $30 for participating in the study. Students who participated in all data gathering phases (2 times) received a gift card of $50 at follow-up. Students accessed SAML and substance abuse prevention education until the end of the semester.

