#### Implementation procedure

As mentioned previously, participants in this study were familiar with e-learning classes and online education due to the COVID-19 pandemic. Educators accessed the web-based educator’s control panel, giving them access to programs. The principal investigator and the research team visited the website. Privacy shields were provided to block their computers or tablet screens from view to ensure confidentiality. Secret ID numbers were used in place of names in chat rooms, and during receiving education programs, admin and educator sessions were offered to students before education. Students were instructed that they could withdraw from the study at any time for any reason. Follow-up questionnaires were completed with paper copies of the pretest questionnaire. After completing the data collection, educators in the intervention group provided substance abuse prevention and SAML education over 3 weeks. It was predicted that the program could be completed in 5 45-min sessions. In the follow-up period, students in the intervention group gave their feedback on the program. Educators returned all completed follow-up questionnaires to administer and Principal Investigator after approximately 3 months. After collecting the follow-up data, educators in the delayed-intervention group could provide SAML and substance abuse prevention education to students and give feedback on their experiences.

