#### Blinding description

Participants were divided into intervention and control groups (delayed-intervention group) after obtaining informed consent. Trials were planned so that participants were aware of all the aims of the study. Based on the research group’s planning, all members of the intervention and delayed-intervention groups accessed all education. The intervention group members were initially educated, and the members of the delayed-intervention group received training 3 months after receiving the post-test results. It is necessary to mention that students were unaware of assignments in the study groups.

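### The Discussion claims the design can evaluate immediate effects, but outcomes are measured only at pretest and at the 3-month follow-up

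*Protocol article*

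**What the plan says.** In the Discussion, the protocol article says the student data collection allows evaluation of the programme's "immediate effects on student outcomes and any behavioral effects during the 3 months after the students receive the program".

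The schedule of outcome data is given in several places, and they agree on two assessments:

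- Aim, design, and setting: "Data were collected from students at 2-time points (i.e., pretest and 3-month follow-up".
- Student measures: "Students completed questionnaires at 2-time points: a pretest and a 3-month follow-up".
- The incentive text after the Fig. 3 caption: "Students who participated in all data gathering phases (2 times) received a gift card of $50 at follow-up".
- The Methods paragraph of the Abstract also names two times, and places the education "between pre-test and 3 months post-test".

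On the programme itself, Implementation procedure says that, once the preceding data collection was complete, "educators in the intervention group provided substance abuse prevention and SAML education over 3 weeks". The same section says "Educators returned all completed follow-up questionnaires to administer and Principal Investigator after approximately 3 months". It also mentions feedback on the programme from intervention students during the follow-up period.

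On the control arm, Delayed-intervention group and Implementation procedure place its training after the 3-month follow-up data are collected. Blinding description says "members of the delayed-intervention group received training 3 months after receiving the post-test results".

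**The concern.** The Discussion sentence attributes a property to the design: that it can show what the programme does at once as well as what follows over 3 months. An immediate effect needs an outcome measurement in both arms at or soon after the end of the programme, and the schedule contains none. At stake is what the trial may conclude. A single between-group difference at 3 months could reflect an early effect that has partly faded, one that has persisted, or one that emerged later. The data cannot tell these apart, and a reader of the Discussion would think they could.

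A lesser matter is that the article does not tie the 3 months to one event. A reader therefore cannot say how long after the programme the follow-up effect is measured.

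**Working it through.** The plan states no figure to reproduce. The check compares the schedule with the claim and then does simple timing arithmetic.

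**Step 1: count the assessments.** The Abstract, Aim, design, and setting, the incentive text and Student measures each give two. One is the pretest, which leaves 2 − 1 = 1 post-baseline assessment. The Discussion later describes the instrument as a pre-post measure, which agrees.

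**Step 2: look for anything else collected near programme end.** The only candidate is the programme feedback. It covers satisfaction, availability and quality of materials, and in the follow-up period it comes from the intervention arm alone. It cannot estimate a between-group effect on intention, willingness, behaviour or media literacy.

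**Step 3: place the one post-baseline assessment.** Inputs: programme length 3 weeks (Implementation procedure); 3 months = 91.3 days / 7 = 13.0 weeks. Assumption: the programme starts straight after pretest.

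| Origin of the 3 months | Weeks from pretest to follow-up | Weeks from programme end to follow-up |
|---|---|---|
| Pretest | 13 | 13 − 3 = 10 |
| Programme end | 3 + 13 = 16 | 13 |

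If the programme started *s* weeks after pretest, the pretest-anchored gap would be 10 − *s* weeks. Follow-up would coincide with programme end only if *s* = 10. Even then there would be one post-baseline measurement, so the immediate and the 3-month effect still could not both be estimated.

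**Step 4: compare the wording on the origin.**

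- Abstract: the education lies inside an interval that opens at pretest.
- Discussion: the period is counted from when students receive the programme, an event that controls do not have before follow-up.
- Implementation procedure: about 3 months, with no starting event named.
- Blinding description: 3 months from the post-test results to the delayed group's training. This dates training, not a questionnaire.

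The text fixes no single origin. The result of Steps 1 and 2 does not depend on which origin is meant.

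**The case against.** The strongest reply is that nothing operational rests on the phrase. It occurs once, in the Discussion. Neither the outcome measures nor the statistical methods define an immediate endpoint, time point or analysis, so the eventual report may never make the claim. It could also be read charitably, with immediate effects meaning knowledge and attitudes, and the 3 months applying to behaviour. The first part stands: this is an error in a statement about the design, not evidence of a faulty analysis. The charitable reading does not rescue the sentence, because attitudes, literacy and behaviour are all measured at the same single follow-up.

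A second reply concerns the time origin. The article is condensed, and Fig. 3, its schedule of enrolment, interventions and assessments, is not shown and may name the origin. That is fair, and it is why the origin is only a request for clarification. A figure that named the origin would not add the missing assessment.

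A reader might go further and infer that the intervention arm is surveyed 3 months after programme end and controls 3 months after pretest. That would put the arms 3 weeks apart, or 3 / 16 = 19% of the longer span, and would confound the effect with calendar time. The documents do not support this. No section sets different dates by arm, all students are given one schedule, and the follow-up questionnaires are described as one return before the delayed group is trained. With a common pretest origin the difference is 0 weeks. The 19% is a share of an assumed span and does not measure bias.

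A reader might also see a third assessment, or a contradiction, in Blinding description. If post-test there means the 3-month follow-up, as it does in the Abstract, then training the delayed group 3 months later still comes after data collection. The passages are then compatible, and the wording is merely unclear.

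**Conclusion.** The claim to evaluate immediate effects is wrong as written. No outcome assessment is described at programme end, and the single post-baseline measurement falls about 10 to 13 weeks after it, assuming the programme begins directly after pretest and 3 months is 13 weeks. The trial can estimate the between-group difference at the 3-month follow-up and cannot separate an immediate effect from it. The conclusion rests on the count of two assessments, on which the sections agree, and not on the effect size, sample size or choice of origin.

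The loose counting of the 3 months is a secondary point of clarity. It leaves the interval between programme and measurement uncertain by about 3 weeks (10 or 13). It is not shown to differ between arms, and no confounding follows from the text.

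**What to change.** 1. In the Discussion, delete the reference to immediate effects. Limit the stated objective and all conclusions to the between-group difference at the 3-month follow-up.
2. State one origin for the 3 months that both arms share, such as pretest, and use it in the Abstract, Implementation procedure and Discussion. If Fig. 3 already names it, align the text with the figure.
3. In Blinding description, say which assessment post-test refers to, and reconcile the timing of the delayed group's training with Delayed-intervention group, Implementation procedure and Student measures.

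The cost is wording only, with no added visit, questionnaire or participant. Keeping the claim would instead require an outcome survey of both arms at programme end. The instrument has about 100 items, and the Discussion already lists its length as a limitation, so narrowing the claim is the cheaper course.
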